## Interventions

3

### Treatment plan

3.1

Both the experimental group and the treatment group will according to the guidelines recommended by “Global strategy for prevention, diagnosis and management of chronic obstructive pulmonary disease (GOLD)”^[3]^ and the “Guidelines for the Diagnosis and Treatment of Chronic Obstructive Pulmonary Disease (2013 Revised Edition)”^[21]^:

Health education: education and urge quit smoking; to understand the pathophysiology and clinical basic knowledge of COPD; to understand the opportunity to seek medical treatment in hospitals; vaccination; to prevent colds and avoid dust, smoke, and harmful gases.

Medication: Tiotropium bromide powder inhalation (Silihua, Boehringer Ingelheim Pharma GmbH & amp; Co.KG [Germany]) 18 μg, inhaled by inhaler once a day.

#### Experimental group

3.1.1

In addition to basic treatment (Health education and Tiotropium bromide), Baduanjin training is also performed. The first week will be supervised and guided by professionals from Chengdu University of Traditional Chinese Medicine to teach Baduanjin (version from the General Administration of Sports). At least 5 days a week, 60 minutes for each training, which can be divided into 30 minutes in the morning and afternoon according to personal tolerance. After the first 2 weeks, the patients will train at home, and they will be given Baduanjin Tutorial CD and exercise card book to record the daily training. From the 3rd week, there will be an intensive training every Sunday. Two professionals will review the record of the exercise card and guide corrective actions until the end of 24 weeks.

#### Control group

3.1.2

The control group members will not receive any training while undergoing basic treatment, and they will be told to maintain the original lifestyle and control the amount of exercise. At the same time, each participant will be issued a daily activity record card to record the number of daily WeChat steps and additional activities.

### Outcome measures

3.2

Primary outcome: The primary outcome is the change in lung function from baseline to the end of the follow-up period (all time points). Including FEV_1_, FVC, FEV_1_/predicted value.

Secondary outcomes: Including COPD assessment test (CAT), 6 minute walking test (6MWT), dyspnea score (modified British medical research council dyspnea score, mMRC), and St. George Respiratory Questionnaire (SGRQ), Self-rating Depression Scale (SDS), Self-rating Depression Scale (SAS).

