**Methods::**

This study is a randomized controlled trial, 192 patients with mild COPD were randomly divided into experimental group and control group. Both of them will receive basic treatment (health education and Tiotropium bromide), the experimental group will receive Baduanjin exercise training, and the control group will be told to maintain the original lifestyle and control the exercise. The Baduanjin exercise will last for 24 weeks and will be followed up for 72 weeks. The primary outcome is the change in lung function, including FEV_1_, FEV_1_/forced vital capacity (FVC), and FEV_1_/predicted. The secondary results included COPD assessment test, 6-minute walk test, St. George Respiratory Questionnaire, and Dyspnea Scale. Safety will also serve as assessing during the test.

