### Design

2.1

This study is a randomized, parallel, and controlled trial designed to evaluate the effectiveness of Baduanjin exercise intervention in improving lung function, exercise capacity, and quality of life in patients with mild COPD. A total of 192 patients will be recruited in Chengdu and randomly assigned to the experimental group or the control group in a 1:1 ratio. Participants in the experimental group will receive a 24-week Baduanjin exercise training intervention at least 5 days a week and 60 minutes a day, while participants in the control group will not be given any specific exercise intervention and will be told to maintain their original lifestyle for 24 weeks. The primary and secondary outcomes will be measured at baseline and at weeks 12, 24, 36, 48, 72, and 96. The participation process of this trial is shown in Fig. 1. This agreement follows the standard agreement item: Intervention Test Recommendation (SPIRIT) guidelines,^[20]^ and meets the SPIRIT list (please see Guidelines Checklist). The study flow chart is presented in Fig. 2.

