### Sample size

2.4

This study is a randomized controlled trial. The experimental group is basic treatment (health education and Tiotropium bromide) + Baduanjin exercise training, and the control group is basic treatment + maintain the original lifestyle and control the exercise. Pulmonary function (FEV_1_%) is the main outcome index. According to previous literature.^[19]^ The mean and standard deviation of FEV_1_% of the control group was 57.09 and 22.53, while the mean and standard deviation of FEV_1_% of the experimental group was 60.24 and 20.15, set *α* = 0.05 (bilateral), *β* = 0.10. The sample size N1 = N2 = 77 cases of experimental group and control group were calculated by Power Analysis and Sample Size version 15.0.5 (PASS 15.0.5 NCSS, LLC USA). Assuming a 20% dropout rate for the study subjects, 96 samples were needed. Therefore, the lowest sample size was 192.

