### Statistical analysis

3.6

All data analysis will be carried out in accordance with the principle of intentional processing. The missing value will be substituted for the last observation carried forward method. Before the analysis, 2 similar participants with complete data will be carefully checked to ensure that the data are correct.

The data will be analyzed using a social science version 22.0 statistical software packages (SPSS 22.0, Chicago, IL). The analysis method will be selected according to the distribution characteristics of the data: the measurement data will be checked using group *t* test or non-parametric test, the count data will be tested using chi-square test or Fisher exact probability method, and the score data will be tested using non-parametric test. Compared with the baseline value, paired *t* test or non-parametric test will be used to evaluate measurement data, and non-parametric test will be utilized to test count data. All statistical tests will be bilateral tests, and a *P* value <.05 will be deemed to indicate statistical significance.

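### The primary outcome is defined inconsistently and spans up to 18 unadjusted tests, so the stated 5% error level is not protected

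*Protocol article*

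**What the plan says.** The protocol article describes the primary outcome in three places.

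- **Abstract, Methods:** "The primary outcome is the change in lung function, including FEV_1_, FEV_1_/forced vital capacity (FVC), and FEV_1_/predicted". No visit is named.
- **Section 2.4, Sample size:** "Pulmonary function (FEV_1_%) is the main outcome index". There is one variable and one comparison, at two-sided alpha 0.05 and beta 0.10. No visit is named, and FEV1% is not defined there.
- **Section 3.2, Outcome measures:** "The primary outcome is the change in lung function from baseline to the end of the follow-up period (all time points", followed by "Including FEV_1_, FVC, FEV_1_/predicted value". The Figure 1 caption gives the same three measures.

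Section 2.1 has the outcomes "measured at baseline and at weeks 12, 24, 36, 48, 72, and 96", which is six visits after baseline. Section 3.6 plans a two-group t test or a non-parametric test for measurement data. It adds "All statistical tests will be bilateral tests" and sets P<.05 as the threshold for significance. It names no primary visit, order of testing, joint or repeated-measures model, or adjustment.

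**The concern.** The three statements cannot all be the primary outcome. FVC and FEV1/FVC are different quantities. Treating one of them as a slip still leaves three primary measures where the sample size allows for one. On timing, section 3.2 first points to the end of follow-up and then, in the same sentence, opens the outcome to every visit.

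Two things are at stake. First, the 5% level applies to each test, not to the trial's conclusion, so the chance of some significant primary result when the exercise does nothing is well above 5%. Second, because the definitions differ, a report could lead with whichever measure and visit looked best and still cite the published protocol in support. The abstract's Discussion already expects the trial to show that the exercise prevents deterioration of lung function, so the weight put on a single positive finding matters.

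**Working it through.** **Step 1. The plan's own figure.** Section 2.4 gives means of 57.09 (SD 22.53) and 60.24 (SD 20.15), alpha 0.05 two-sided, power 90%, and 77 per arm.

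- Difference = 60.24 − 57.09 = 3.15.
- Root-mean-square SD = √((22.53² + 20.15²)/2) = 21.37.
- n per arm = 2 × SD² × (1.960 + 1.282)² / difference² = 2 × 21.37² × 10.51 / 3.15² ≈ 968.

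The stated 77 does not reproduce. With 77 per arm, power for 3.15 points is about 15%. The dropout step is nearly right: 77/0.8 = 96.25, against 96 stated. This is a separate problem, but it bears on the fix. The calculation allows for one comparison only.

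**Step 2. Count the tests.** Visits: weeks 12, 24, 36, 48, 72 and 96, so 6.

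| Source | Measures | Tests if every visit counts |
|---|---|---|
| Abstract | FEV1, FEV1/FVC, FEV1/predicted | 3 × 6 = 18 |
| Section 3.2 | FEV1, FVC, FEV1/predicted | 3 × 6 = 18 |
| Section 2.4 | FEV1% | 1 × 6 = 6 |

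These are alternatives, not sets to be added together.

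**Step 3. Independent tests, as an upper reference.** With no effect, the chance of at least one two-sided P<.05 among k tests is 1 − 0.95^k. In the benefit direction it is 1 − 0.975^k.

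- k = 18: 1 − 0.95^18 = 60.3%; benefit direction 1 − 0.975^18 = 36.6%.
- k = 6: 1 − 0.95^6 = 26.5%; benefit direction 1 − 0.975^6 = 14.1%.

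**Step 4. Correlated tests.** The article gives no correlations, so these are assumed. Normal test statistics were simulated under no effect (400,000 draws), with equal correlation between visits, equal correlation between measures, and their product across different measures at different visits.

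| Correlation between visits | Correlation between measures | 18 tests, two-sided | 18 tests, benefit only | 1 measure × 6 visits, two-sided | 1 measure × 6 visits, benefit only |
|---|---|---|---|---|---|
| 0.5 | 0.5 | 45% | 23% | 21% | 10% |
| 0.5 | 0.9 | 32% | 16% | 21% | 10% |
| 0.8 | 0.5 | 32% | 16% | 14% | 7% |
| 0.8 | 0.9 | 22% | 11% | 14% | 7% |
| 0.95 | 0.9 | 14% | 7% | 9% | 4% |

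The last row is an extreme case. It shows that 22% is not a floor. The shared baseline and the last-observation-carried-forward rule in section 3.6 both push the correlation between visits upward.

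One measure tested once at one visit gives 5% two-sided and 2.5% in the benefit direction.

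**The case against.** **Condensation.** An abstract is a summary, the Figure 1 caption agrees with section 3.2, and "is the main outcome index" in section 2.4 could mean the lead measure within a family. That narrows the outright conflict to FVC against FEV1/FVC. It does not remove it, and it does not explain why three primary measures at every visit are sized as one comparison.

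**Left to an analysis plan.** Multiplicity rules often sit in a SAP or full protocol, and neither is shown. Their absence alone would be no finding. The point rests on what is stated: differing outcome lists, every visit made primary, and one threshold for all tests. A later document could add a hierarchy, but it would not make the published sections agree.

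**Stronger readings.** A reader might infer three things that the document does not support.

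- *That one P<.05 among the 18 counts as success under the plan.* No success rule is written, and testing visit by visit is itself inferred from sections 3.2 and 3.6 together. The supportable statement is that the plan does not prevent it.
- *That a false claim of benefit has a 22-45% chance.* Those figures count both directions. Benefit alone is about half that, against a nominal 2.5%.
- *That there are 24 primary tests.* That count merges the abstract's list with that of section 3.2. No stated definition contains four measures.

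**Conclusion.** The point stands as an inconsistency in the primary outcome combined with a stated testing rule that does not hold the overall error at 5%.

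For three measures at six visits, the chance of at least one two-sided false-positive result is about 22-45% under the assumed correlations, with 60% as the independent reference and about 14% in the extreme case. In the benefit direction it is about 11-23%, or 7% in the extreme case, against 2.5%. If only the sizing variable counts, six visits give about 14-21% two-sided and 7-10% for benefit.

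The sizes depend on correlations that the article does not give and on the inferred visit-by-visit testing. The inconsistency depends on neither. It should be settled before any outcome data are seen.

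**What to change.** Use one identical definition in the abstract, section 2.4 and section 3.2. It should name one measure at one visit as the single primary endpoint: the between-group difference in change from baseline, tested once at two-sided 0.05.

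- **Measure.** FEV1 % predicted fits the sizing, provided the sponsor confirms that this is what FEV1% means in section 2.4.
- **Visit.** Either week 96, the end of follow-up, or another single visit fixed before any outcome data are seen. Section 3.2 does not settle this, because it qualifies the end of follow-up with every time point. Week 96 falls 72 weeks after training ends, when carrying forward the last observation may have most to fill in.
- **Everything else.** Make the other lung-function measures and visits secondary, either tested in a stated fixed order or reported as estimates with confidence intervals and no significance claim. Limit the P<.05 sentence in section 3.6 to match.

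The cost is a protocol amendment, which under section 2.2 needs renewed ethics approval, and an update of the registry entry. Only one result will then be confirmatory. The sample size must also be restated for the chosen endpoint, because 77 per arm does not follow from the inputs in section 2.4. No treatment or visit changes.

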### Compliance

3.3

In this trial, compliance was quantified by participation in collective training and exercise book recording. The researchers will make every reasonable effort to follow the patients during the study. Messages will be sent via WeChat or over the phone at each training and follow-up session. Patients with a total time of >80% recorded in the collective training and exercise card will be considered as compliant.

### Safety assessment and adverse events

3.4

During each intensive exercise, we will monitor the heart rate and blood pressure, and ask for details of adverse events such as muscle strain, falls, dizziness, dyspnea, psychological pressure, or COPD exacerbation, etc. For any symptoms identified, we will further document their relevance to the intervention, determine the required changes in treatment depending on severity, and provide further medical care. For hospitalization and emergency visits, we further determined the outcome of the discharge diagnosis and the main cardiopulmonary examination or procedure performed. During the intervention process, any adverse events will be recorded in the CRF and reported to the Steering Committee and the Ethics Committee within 24 hours. If any severe adverse events occurring, training will be discontinued, and reported to the Ethics Committee and receive appropriate treatment.

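### The only adverse-event enquiry the article states takes place at sessions held in the Baduanjin arm alone, so a between-arm comparison of non-serious events would carry ascertainment bias

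*Protocol article*

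**What the plan says.** Section 3.4 (Safety assessment and adverse events) ties the asking to the training sessions: "During each intensive exercise, we will monitor the heart rate and blood pressure, and ask for details of adverse events". The events it lists include COPD exacerbation, falls, dyspnea and dizziness, as well as muscle strain.

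Section 3.1.1 (Experimental group) says when these sessions happen: "From the 3rd week, there will be an intensive training every Sunday". They continue until week 24. Section 3.1.2 (Control group) says: "The control group members will not receive any training while undergoing basic treatment". The control arm's diary covers activity and names no symptoms: "each participant will be issued a daily activity record card to record the number of daily WeChat steps and additional activities".

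On recording, section 3.4 says: "During the intervention process, any adverse events will be recorded in the CRF". On duration, the abstract says: "The Baduanjin exercise will last for 24 weeks and will be followed up for 72 weeks". Section 2.1 (Design) gives both arms a common visit schedule, but for efficacy measures: "The primary and secondary outcomes will be measured at baseline and at weeks 12, 24, 36, 48, 72, and 96". The abstract adds a commitment on safety: "Safety will also serve as assessing during the test". Section 3.2 lists neither safety nor exacerbation among the primary or secondary outcomes.

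**The concern.** Many non-serious events come to light only when someone asks. If one arm is asked every week and the other has no stated enquiry, the recorded counts reflect the frequency of asking as well as the frequency of events. Several of the listed events, such as dizziness, dyspnea, falls and exacerbation, are not specific to exercise and can occur just as readily in controls.

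Two misreadings would follow. Baduanjin could appear to cause events that were merely detected more often, or a real reduction in mild or moderate exacerbations could be hidden. Either would matter for a trial meant to support a simple home exercise as a rehabilitation measure in mild COPD. Separately, the stated recording window leaves most of follow-up without a stated rule for either arm.

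**Working it through.** The article gives no figure for event ascertainment, so there is none to reproduce. The check has two parts: a count from the stated schedule, and an illustration that rests on assumptions.

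**1. Count from the stated schedule**

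| Item | Baduanjin | Control | Source |
|---|---|---|---|
| Stated adverse-event enquiries | 24 − 3 + 1 = 22 Sundays | 0 stated | 3.4, 3.1.1, 3.1.2 |
| Stated recording window | 24 weeks | 24 weeks | 3.4, abstract |
| Total time in study | 24 + 72 = 96 weeks | 96 weeks | abstract, 2.1 |
| Share of time inside the window | 24/96 = 25% | 25% | |
| Share of time outside the window | 72/96 = 75% | 75% | |
| Post-baseline outcome visits | 6 | 6 | 2.1 |

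The window is the same length in both arms. It is therefore a gap in coverage and not in itself a source of between-arm bias. The bias comes from the first row.

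**2. Illustration (capture rates and true risks are assumed; the article gives neither)**

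Observed risk = true risk × capture probability, so observed ratio = true ratio × (capture in Baduanjin ÷ capture in control).

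Equal true risk, 80% capture in the Baduanjin arm:
- control capture 60%: 0.80/0.60 = 1.3
- control capture 40%: 0.80/0.40 = 2.0
- control capture 30%: 0.80/0.30 = 2.7

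Equal true risk, 90% capture in the Baduanjin arm, 96 per arm with no losses, two-sided 5% test:

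| Control capture | Observed ratio | Chance of a false significant difference, true risk 10% | 20% | 30% |
|---|---|---|---|---|
| 70% | 0.9/0.7 = 1.29 | 7% | 11% | 16% |
| 50% | 0.9/0.5 = 1.80 | 19% | 36% | 53% |
| 30% | 0.9/0.3 = 3.00 | 42% | 73% | 91% |

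True one-third reduction with Baduanjin (ratio 0.67), 90% capture in that arm:
- control capture 90%: 0.67 × 0.9/0.9 = 0.67, correctly shown
- control capture 60%: 0.67 × 0.9/0.6 = 1.0, the benefit disappears
- control capture 50%: 0.67 × 0.9/0.5 = 1.2, the benefit looks like harm

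**3. Under a common schedule**

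The same questions at the six post-baseline visits give 6 enquiries in each arm over 96 weeks. If capture is then equal, the ratio of captures is 1 and the observed ratio equals the true one.

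**The case against.** The article does not say that controls are never asked. Its recording rule covers any adverse event without naming an arm. Section 3.4 also follows up hospital and emergency visits without limiting this to one arm, and section 2.9 records reasons for withdrawal for all participants. The SPIRIT schedule in Figure 1 is not shown and might carry a safety row. Both arms have six visits, and section 3.3 mentions messages or calls at follow-up. The recording sentence may describe the 24-hour reporting duty and not close the window at week 24. Section 3.6 names generic tests and no adverse-event comparison. Much of section 3.4 reads as exercise-safety monitoring, which naturally happens where exercise is supervised.

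Most of this stands, and it limits the claim. A reader might infer that controls are never asked and that nothing is recorded after week 24. The text supports only that no such enquiry or recording is stated. A reader might also infer that the arms cannot be compared on safety at all. That goes too far, because serious events may surface in both arms through hospital care or withdrawal. Nor is it shown that unequal detection leads to unequal withdrawal: the criterion in section 2.9 is a severe exacerbation, the kind least dependent on weekly questioning.

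The objection does not remove the core. The article is not merely silent on a detail that a fuller protocol might supply. It states a collection procedure, and that procedure differs by arm. The visits in section 2.1 are described for efficacy outcomes, the contacts in section 3.3 appear under compliance with no event question, and no text shown gives controls an equivalent enquiry.

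**Conclusion.** The concern holds in a limited form. The one stated enquiry reaches Baduanjin patients about 22 times and controls not at all, and the one stated recording window covers 25% of the 96 weeks. Any between-arm comparison of non-serious adverse events, or of mild to moderate exacerbations, would therefore carry ascertainment bias. The likely direction is against Baduanjin, on the assumption that asking raises capture.

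The size is unknown. The ratios of 1.3 to 3.0 and the false-positive chances are arithmetic on assumed capture rates and true risks; they show what unequal capture could do and do not estimate it. The specified primary and secondary outcomes are not shown to be affected. The point still deserves correction, because the article commits to assessing safety and the remedy is small.

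**What to change.** In section 3.4, state that both arms will be asked the same adverse-event and exacerbation questions at the existing week 12, 24, 36, 48, 72 and 96 visits, and that events will be recorded in the CRF through week 96. Base any between-arm safety comparison on this common schedule alone. Report findings from the Sunday sessions (heart rate, blood pressure, exercise-related events) separately, as monitoring of the training arm. If Figure 1 or the full protocol already schedules such an enquiry for both arms, say so in section 3.4.

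The cost is one short questionnaire and one CRF page at visits that already take place. No treatment changes. Visits 12 or 24 weeks apart will miss some minor events through recall, but the interval is the same in both arms.

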### Data management and quality control

3.5

All records will be collected in the CRF and completed by trained and qualified investigators. After the CRF is accomplished, if any corrections are made, the original record will not be changed. The clinical inspector will review the completed CRF. Data input and management will be carried out under the guidance of medical statistics experts. In order to guarantee the accuracy of the data, two data administrators will input and proofread the data separately. After checking and confirming that the established database is correct, the data will be locked by the main researchers and statistical analysts. Locked data or files will not be changed from now on and will be submitted to the research team for statistical analysis. Sichuan Evidence-based Medicine Center of Traditional Chinese Medicine (Chengdu, China), which has no conflicts of interest, will monitor the data. The scientific research room of Chengdu University of Traditional Chinese Medicine Hospital, which is independent of researchers, will conduct data review during the experiment.

